**Figure 3 figure3:**
[figure not shown]
The flow of data collection and analysis for the CHILD-MHL scale. MHL: mental health literacy.

### Assessment: cRCT and Semistructured Interviews

#### Implementing the cRCT

We will conduct the cRCT in a minimum of 16 new classes, representing all typologies under the study, from different schools: 4 REP, 4 rural, 4 urban, and 4 private ones (quota sampling). Feasibility will be a major criterion for participant inclusion. Therefore, a minimum of 400 children will be involved in this small-scale cRCT, which is a substantial sample size, as the literature suggests a minimum of 300 participants is sufficient for a cRCT in children [71]. Furthermore, a limited number of participants will allow us to explore in depth the mechanisms influencing the effectiveness of the intervention by analyzing results for each class.

Classes will be randomly assigned to either the intervention group or the control group (on a waiting list without engaging in any activities). Randomization will involve creating matched pairs based on class types, such as pairing 1 urban school class with the intervention and 1 urban school class without the intervention. The CHILD-MHL scale will be administered 1 week before and 2 weeks after the intervention in all classes. We will collect covariates related to children and their environment, including sex, age, school characteristics (geographical and socioeconomic area, population density), parental background (at least one parent not being French, divorced/separated parents), family size (number of siblings), and self-perceived health and emotional status measured by the KIDSCREEN-10 [70]. If possible, with parental consent, teachers will be asked to report whether there is at least one child with a diagnosed mental health problem in the class and provide information on the parents’ socioeconomic situation. Macro-level data will be also included in the analyses (eg, precariousness indexes). The data from the second administration may offer insights into the intervention’s potential impact on children’s well-being and help-seeking actions. Furthermore, participants who received the intervention will respond to closed-ended questions regarding their intention to help someone with a problem, seek help, and their ability to apply strategies for feeling better and recognizing signs of personal distress. The statistical analysis plan will encompass mixed linear models, multilevel models, descriptive statistics, and random effects, with an intention-to-treat primary analysis.

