**Methods:**

Our study focuses on children aged 9-11 years attending primary school classes in various settings, including urban and rural areas, and priority education zones within a French department. Using a participatory research approach, we will conduct workshops involving children, parents, teachers, and 1 artist to cocreate an intervention comprising multiple tools (eg, a pedagogical kit and videos). This intervention will undergo initial evaluation in 4 classes through observations, interviews, and satisfaction questionnaires to assess its viability. Concurrently, the artist will collaborate with children to create the initial version of the CHILD-MHL scale, which will then be administered to 300 children. Psychometric analyses will validate the scale. Subsequently, we will conduct a cluster randomized controlled trial involving a minimum of 20 classes, using the CHILD-MHL scale scores as the primary end point to evaluate the intervention’s efficacy. Additional interviews will complement this mixed methods evaluation. Both the intervention and the scale are grounded in the Child-Focused MHL model.

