#### Validation of the CHILD-MHL Scale

We will use a specific procedure called COSMIN (Consensus-Based Standards for the Selection of Health Measurement Instruments) [67] for scale validation. The questionnaire including the scale and other variables of interest will be initially administered to children from 10 classes from different schools (ie, around 250 children). Half of these classes are those of the viability evaluation. The sample size of 250 respondents is acceptable, considering feasibility and following the rule of thumb of 10 respondents per item [68]. Besides, feasibility must be considered for data collection. Data will be recorded on a tablet for each child consecutively, with supervision provided by the principal investigator and the research assistant. The research assistant will be the only person in possession of a document containing the child’s name and the corresponding code, allowing for matching the questionnaire administrations. The data from the initial administration will be analyzed to assess the scale’s dimensionality and whether the 60 items adequately cover the 6 dimensions of the Child-Focused MHL model. Exploratory and confirmatory factor analyses will be performed. At this stage, it will be possible for the consortium to add or remove items to cover the 6 dimensions.

After 3 months, the questionnaire with the scale, which might have been modified, will be readministered for the second time to all 250 children from the 10 classes during the week preceding the start of the viability evaluation intervention. This second data collection is essential if the scale has been modified and is highly recommended to refine the scale dimensions. Using this large data set, analyses will be performed to reduce the number of items by employing the Classical Test Theory and the Item Response Theory [69]. Exploratory and confirmatory factor analyses will be performed again to assess the dimensionality and structural validity of the scale. For the convergent and discriminant validity of the scale, the questionnaire will include other variables, including, sex, age, or emotional status measured by the KIDSCREEN-10 [70]. We will check for variations in the scores of scale dimensions among different groups.

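### The cRCT's size is justified by counting children, although classes are randomised; the claim that 300 participants suffice is unsupported as written

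*Protocol article*

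**What the plan says.** The section Implementing the cRCT makes the class the unit of allocation: "Classes will be randomly assigned to either the intervention group or the control group". Allocation is matched: "Randomization will involve creating matched pairs based on class types". On the number of clusters it says: "We will conduct the cRCT in a minimum of 16 new classes, representing all typologies under the study, from different schools". The Methods paragraph of the Abstract gives a different minimum: "we will conduct a cluster randomized controlled trial involving a minimum of 20 classes".

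Two reasons are offered for the size. The first is practical: "Feasibility will be a major criterion for participant inclusion". The second is a benchmark. The section says that "a minimum of 400 children will be involved in this small-scale cRCT", and describes this as "a substantial sample size, as the literature suggests a minimum of 300 participants is sufficient for a cRCT in children".

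The article states no ICC, design effect, target effect, SD, significance level or power for the cRCT. The same section does plan mixed and multilevel models with random effects, and measures the CHILD-MHL score before and after the intervention in all classes.

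**The concern.** The benchmark is expressed in children, but the trial allocates classes. Children in one class share a teacher, a school and the delivery of the intervention, so their scores are likely to be correlated, and each further child in the same class adds less information than a child in a new class. A threshold given only as a number of participants cannot tell a few large classes from many small ones, although these designs differ in precision.

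The point is not that a sample size calculation is absent; a condensed article may leave that to a fuller document. The article makes a positive statement of sufficiency, and the reason it gives does not fit the unit randomised.

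The CHILD-MHL score is the primary end point, and the Conclusions say the findings will guide how far the intervention is rolled out. Readers should know what size of effect the comparison can detect. A description resting on a head count suggests more precision than 16 classes may give.

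**Working it through.** **Inputs from the article**
- Classes: minimum 16 (Implementing the cRCT) or minimum 20 (Abstract).
- Children: minimum 400.
- Class size: 400/16 = 25. This agrees with the validation study, where the scale is "initially administered to children from 10 classes from different schools (ie, around 250 children"): 250/10 = 25. The viability pilot implies larger classes (130/4 = 32.5); 25 is used here because it reproduces the stated 400.
- Allocation in matched pairs, so k = 8 classes per arm with 16 classes, or k = 10 with 20.

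**Assumptions (not in the article)**
- ICC 0.01 to 0.20.
- Two-sided 5% significance level, 80% power.
- No dropout and equal class sizes, both of which favour the plan.

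**Step 1: the plan's own figure.** 16 × 25 = 400. The head count reproduces exactly. The sufficiency statement cannot be reproduced, because no effect, SD, ICC or power is attached to it.

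**Step 2: what a head count would mean for independent children.** The detectable effect is 2.80 × √(4/N). For N = 400 this is 0.28 SD; for N = 300 it is 0.32 SD.

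**Step 3: why a head count is not enough.** With design effect DE = 1 + (m − 1) × ICC and ICC 0.10:
- 300 children in 12 classes of 25: DE = 1 + 24 × 0.10 = 3.4, so 300/3.4 = 88 effective children.
- 300 children in 60 classes of 5: DE = 1 + 4 × 0.10 = 1.4, so 300/1.4 = 214 effective children.

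The number of participants is the same, but the information differs about 2.4-fold (214/88).

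**Step 4: the planned design.** With m = 25, DE = 1 + 24 × ICC and effective N = 400/DE. In SD units, SE = √(2 × DE/(k × 25)). The detectable effect is the value giving 80% power under the noncentral t distribution. For k = 8 and 14 df it equals 3.01 × SE. Worked case at ICC 0.05: DE = 2.20, SE = √(4.40/200) = 0.148, detectable effect 3.01 × 0.148 = 0.45 SD.

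| | ICC 0.01 | ICC 0.05 | ICC 0.10 | ICC 0.20 |
|---|---|---|---|---|
| Design effect | 1.24 | 2.20 | 3.40 | 5.80 |
| Effective N, 16 classes | 323 | 182 | 118 | 69 |
| Detectable effect (SD), 16 classes, unadjusted, 14 df | 0.34 | 0.45 | 0.56 | 0.73 |
| Detectable effect (SD), 16 classes, paired analysis, 7 df, no gain from matching credited | 0.36 | 0.49 | 0.60 | 0.79 |
| Detectable effect (SD), 20 classes, unadjusted, 18 df | 0.30 | 0.39 | 0.49 | 0.64 |
| Detectable effect (SD), 16 classes, baseline adjustment assumed to halve the variance, 14 df | 0.24 | 0.32 | 0.39 | 0.51 |
| Power for 0.3 SD, 16 classes, unadjusted, 14 df | 71% | 47% | 33% | 21% |
| Power for 0.5 SD, 16 classes, unadjusted, 14 df | 99% | 88% | 71% | 49% |

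**Step 5: where effective N passes 300.** 400/(1 + 24 × ICC) = 300 gives ICC = (400/300 − 1)/24 = 0.014. Above that ICC, the 400 children carry less information than 300 independent children.

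**The case against.** Several points on the other side are sound.

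- **The trial is presented modestly.** The section calls it small-scale and says feasibility drives inclusion. A feasibility rationale would be acceptable by itself. The difficulty is that the same passage goes on to claim sufficiency on another ground.
- **Clustering is not ignored overall.** Multilevel models with random effects are planned, and classes are matched by type. This stands, and it confines the point to the sizing. A correct analysis will reflect the limited number of classes, but it cannot add information.
- **The cited source may have allowed for clustering.** The benchmark is worded as applying to cluster trials in children, and the source cannot be checked here. It would therefore be wrong to say that the source is mistaken. Even so, a threshold quoted without number of classes, class size or ICC cannot be carried over to 16 classes of 25.
- **Unadjusted figures for 16 classes understate what may be achieved.** A baseline score is collected, the Abstract gives 20 classes, both class counts are minimums, and the ICC may be low. All of this is fair, and the table shows these cases. The paired analysis moves the figures the other way.

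A reader might infer that the trial is underpowered, or that it lacks the size it claims. The documents do not support that. The size claimed is 16 classes and 400 children, which agrees arithmetically, and no power or detectable effect is claimed anywhere. For 0.5 SD at ICC 0.05, unadjusted power is 88%. A reader might also infer that a null result would be taken as proof of no effect. The article does not say so, and it plans to combine the cRCT with interview and viability data.

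**Conclusion.** The sufficiency statement is unsupported as written: it compares a number of children with a number of children, whereas precision here depends mainly on 8 (or 10) classes per arm and on an unstated ICC. Whether the design is adequate cannot be settled from the article. Across the cases shown for an assumed ICC of 0.01 to 0.20, the detectable effect runs from 0.24 SD (16 classes, low ICC, adjustment halving the variance) to 0.79 SD (16 classes, high ICC, paired analysis without adjustment). The design is thus adequate for larger effects at low ICC and inadequate for smaller effects at higher ICC. These figures depend on the assumed ICC range, 80% power, a two-sided 5% level, 25 children per class and no dropout. The unreconciled minimums of 16 and 20 classes matter because they alone move the unadjusted figure at ICC 0.05 from 0.45 to 0.39 SD. The point calls for a correction to the justification, not for a new design.

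**What to change.** 1. Reconcile the minimum number of classes between the Abstract (20) and Implementing the cRCT (16), and restate the number of children to match.
2. Delete the claim that 300 participants is sufficient, and describe the trial as sized by feasibility.
3. State a cluster-based detectable effect for the agreed number of classes over an ICC range labelled as assumed. Base it on an analysis adjusted for the pre-intervention CHILD-MHL score, with degrees of freedom that match the planned treatment of the pairs.
4. Before the cRCT starts, update that figure with the class ICC and pre-post correlation from the 10 validation classes. Ten classes give an imprecise ICC, so report it with its interval. Because items may change between administrations, compute the correlation only where the same version of the scale was used.

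The cost is one rewritten paragraph and two estimates from data already planned. No extra classes are required. The drawback is that the stated adequacy will look less favourable than the present text suggests.

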#### Conducting Semistructured Interviews and Analyzing Data Through Mixed Methods

This phase marks the conclusion of the project, during which we will gather and collate all data to demonstrate the effectiveness of the intervention in improving children’s MHL. We will conduct semistructured interviews with a deliberate selection of 30 pupils and 10 parents from various schools participating in the cRCT. All teachers of involved classes will be also interviewed. These stakeholders will comment on the effects of the intervention on children’s attitude toward mental health: self-perceived benefits of the intervention, what children have learned, and how they will reuse their new knowledge and competencies (from help-seeking to detection of a mental health problem). Interview texts will be coded and treated per theme. Quantitative and qualitative data, collected separately, will be combined and analyzed using a convergent design [72]. When combining the data, we will also consider contextual factors, location, the study population, and other relevant elements that might influence the results. The mixed methods analysis will provide a comprehensive understanding of the intervention.

### Ethics and Regulatory Affairs

Given that children constitute a vulnerable population with limited autonomy, we will implement stringent measures to safeguard their well-being. The CHILD-MHL scale itself should not raise any privacy concerns as it does not collect private or sensitive information. However, variables such as emotional status or self-perceived mental health may introduce potential delays in the procedures. Their inclusion in the questionnaire will be thoroughly justified, but if collecting these data proves challenging, we will rely exclusively on macro-level data (eg, school geographical area, class size) for analysis.

Quantitative data will be collected through a secure tablet-based self-administration software, while qualitative data will be gathered via recorded interviews and subsequently transcribed. We will conduct a Privacy Impact Assessment (PIA) and risk analysis. Additionally, a data management plan will be established to outline data handling procedures throughout and after the project, covering collection, storage, analysis, preservation, and sharing. All collected data will be anonymized.

### Ethics Approval

Ethical approval for the study is going to be obtained from the People Protection Committee (Comité de Protection des Personnes), which is the French Ethical Review Authority. We will strictly adhere to the requirements of the Helsinki Declaration for research involving humans. As a systematic examination of ethical considerations is also needed in the survey study, additional ethical approval will be sought from external researchers. We will make sure that project staff are trained and supervised on ethical issues, with specific attention paid to collecting data from children. In case participants (children, parents, or teachers) have questions, the contact information of the responsible researchers will be provided. In the information letter, study participants will be informed about confidentiality and their right to withdraw from the study at any time. The letter will be adapted for young people. All data will be collected and stored in compliance with the requirements of the Ethical Review Authority and the GDPR (General Regulations for the Protection of Personal Data), as well as the French National Commission on Informatics and Liberty (Commission nationale de l'informatique et des libertés).

## Results

After obtaining the ethical approval, data collection and analyses will be conducted from March 2024. The first paper is expected to be submitted at the beginning of 2025. Finally, the results from all parts of the study will be synthesized in 2026.

We started working on the project in 2022 to predefine some contents and tools. The first tool of the intervention is the pedagogical kit Le Jardin du Dedans, supported by the public organization Psycom Santé Mentale Info and endorsed by UNICEF France. The kit is composed of 12 storyboards introducing MHL to children through an animated story. Each storyboard corresponds to a drawing with specific text. Two manuals are given to educators (eg, teachers, parents) to animate the story and discuss its content with children through tips and key messages. The animation includes 3 sessions conducted in 2 weeks covering the 12 storyboards. Le Jardin du Dedans is based on a metaphor stating that mental health is like an inner garden that we need to take care of across all seasons, from joyful summer to dark winter.

The second tool is a handbook that is addressed to teachers to sensitize them to children’s mental health problems. In 35 pages, teachers are taught the meaning of mental health, the importance of well-being in school, child development and related influences, and main emotional and behavioral disorders (from anxiety disorder to autism spectrum disorder). After reading it, teachers are expected to feel empowered and more confident in dealing with children with mental health problems. The handbook is produced by the Pan American Health Organization and the WHO.

In a 5-page leaflet produced by the nongovernmental organization The Ink Link, children become acquainted with the notion of MHL by discovering its 6 dimensions. Each dimension is illustrated by some examples (eg, the description of mental health professionals and risk and protective factors).

We have also compiled the initial list of items (n=56) for the scale. These 56 items were listed by 2 public health researchers, and revised by 11 experts in the field of child health, including child psychiatrists and developmental psychologists. These items will then undergo further review by a panel of at least 30 experts, including psychologists, educators, and public health researchers. Following this selection process, 1 artist will collaborate with children to illustrate the items. Subsequently, the scale will be administered to several hundred children to collect data for psychometric analyses.

Finally, we compiled a report listing the existing education policies for children’s mental health in France.

## Discussion

### Anticipated Findings

We have started cocreating the intervention to increase children’s MHL. The current partial intervention is composed of 3 tools: a pedagogical kit, a handbook, and a leaflet. In the cocreation process, experts provided the contents of each tool, and artists shaped/transformed them into visually appealing illustrations. These tools were tested with small groups of children and teachers to gather feedback; particularly, the pedagogical kit was animated in several classrooms, the handbook was proofread by teachers, and the leaflet underwent refinement in a classroom setting. The involvement of renewed institutions, namely, UNICEF France, the Pan American Health Organization/WHO, and the nongovernmental organization The Ink Link, ensures a solid foundation for this global intervention [73].

The inclusion of children, teachers, and parents from the outset of the cocreation process proved challenging due to their availability and time constraints, which often conflicted with project funders’ requirements and local service expectations, such as school complexes. These challenges align with findings in the literature [74,75], with logistics and timeline management being the most commonly cited difficulties. However, our study is among the few to employ cocreation with children on a sensitive topic such as mental health, allowing them to play an active role in designing and producing a health-related intervention [76]. Moving forward, our goal is to involve all stakeholders in the cocreation process from the project’s inception.

Few multitool interventions, especially those involving the target audience and the child’s environment, including teachers and parents currently exist [55,77]. Accordingly, we have adhered to a whole-school approach to enhance the tool’s effectiveness. Additionally, it is worth noting that the theory of MHL remains unaddressed in existing interventions.

Usually, only 1 type of support is used (eg, videos or courses). The novelty and uniqueness of our intervention lie in the integration of several tools, potentially enhancing its acceptability and effectiveness [78].

Once all the tools are produced, they will be pieced together and evaluated. Data from viability assessment, cRCT, and interviews will be combined through a mixed methods approach to produce the most accurate evidence [79]. Initial testing of the first tools has shown promising results, particularly with positive feedback from children regarding the pedagogical kit. Furthermore, we have initiated contact with schools to collect data, and the project is gaining recognition within the French academies.

Simultaneously, we have begun developing the scale. Following a rigorous approach, we plan to create an initial version of the scale that aligns with the dimensions of the Child-Focused MHL model. According to the guidelines for scale development [80], the first essential step involves defining a substantial number of items that capture the concept being measured. To ensure content validity (ie, the adequacy with which a measure assesses the domain of interest [81]), we have engaged one of the founders of the Child-Focused MHL model in the item inventory process.

In the end, conducting an inventory of policies in the French academies related to educational programs for children’s mental health is crucial to gauge the acceptability of our intervention. We will assess whether the intervention is more effective in schools with existing mental health programs and a general sensitivity to this topic [82]. Thus, we have initiated a viability evaluation to provide initial evidence on the factors, such as policies, influencing the adoption of the intervention in real-life conditions.

